### Materials

Materials to be used in each of the four main stages, as shown in Fig 2, are described as follows.

**Fig 2 pone.0313478.g002:**
[figure not shown]
AT materials. Study materials are shown as to be used in each stage of research. First stage is the development of the training tools in Unity. Second stage is the application of auditory assessment for auditory processing screening which will be managed in two sessions of 50 minutes. Third stage refers to the application of auditory training during 15 hours. Fourth stage refers to the data management.

ADT Game will be developed to enhance user experience and favor attention through task engagement. ADT Game will consist in basic sound features discrimination training (pitch, intensity, duration and localization). Each participant will use personal computer and calibrated headphones to receive training. For auditory game-based and non-game-based training, Unity Software and IDE Visual Studio Code (C#) will be used to generate stand-alone applications for both Windows and Mac OS.

For neuro-audiological assessments audiometer Interacoustics AD226 with audiometric headset DD45 and B71 Bone conductor will be used to conduct pure-tone tests and Unicorn Hybrid Black 8-channel EEG (250 Hz), with electrode placement using the 10–20 system, and calibrated headphones Senheisser SRH440 (10–22,000 Hz) will be used to manage AEPs.

A brief basic auditory discrimination performance questionnaire (ADPQ) was designed for addressing participant’s discrimination and complementary conditions during and after each of experimental acoustic features under attentive processes. Questionnaire (I-CVI > 0.875) consists of 7 items evaluating in a 4-point likert scale the performance status of the participant (perceived state and perceived performance). This questionnaire helps the present study to have a perceptual participant’s discrimination response and to reduce participant’s state bias during the assessment.

For acquisition software, OpenVibe will be used to record EEG signals and Built-in App developed in Super Collider will be used for sound reproduction using a self-designed application to make easier the adjustment of multiple acoustic feature paradigms.

For data software, EEGLAB Matlab toolbox will be used for processing and analysis of EEG recorded data. Matlab software will be used for data analysis obtained from participants performance during training and as result of the auditory assessments.

### Study design & setting

This work is divided in three instances: 1) development and validation of the digital game, 2) implementation and evaluation of the ADT game performance in auditory improvement, 3) comparison between both methodologies.

The first stage consists of serious game development. This stage is divided into two sub-stages. First one is back-end development (auditory tasks) and tests and second one is front-end development (interactive elements) and tests, additionally both are having their respective correction sub-stages.

Second stage consists in the implementation of the game-based ADT, as described in Fig 3. In 30-minutes sessions (15 hours total), the 40 participants will be treated by ADT; 20 participants will use the game-based and 20 participants will be treated by a non-game-based training procedure with the same four modules in both cases. Both procedures will locally save training data in participant computer, which will be gathered each week.

**Fig 3 pone.0313478.g003:**
[figure not shown]
Protocol steps. 1) Game-Based AT is first developed and validated through perceived usability evaluation questionnaires. 2) Assessments are done before and after AT is implemented for two sample groups. 3) Finally AT effectiveness is measured and compared through groups performance and AEPs.

The participant will be introduced to the study, explaining to them the informed consent and the confidentiality criteria. Participants will be given their audiometry results and a beginner game kit, also they will receive an online-shop gift card ($5-$25 us) if they finish the training levels satisfactorily, based on constant and consistent game playing, meaning they accomplish daily training and completely succeed in all training levels. Participants will also receive hearing health information after intervention and the option of scheduling a medical appointment with the otorhinolaryngologist and/or audiologist if they desire.

Auditory assessments will be conducted in noise-controlled rooms within university buildings or hospitals. Eligibility screen, informed consent and pure tone audiometry will be carried before allocation. Procedure to follow will be explained to them, beginning the pure-tone audiometry (air and bone) procedure. The participant will be indicated to raise the hand when they start to listen to the stimuli.

Then, they will be introduced to the electrode placements. Electrodes (Fz, F3, F4, Cz, C3, C4, T7 & T8) will be placed, and conductive gel will be applied to reduce the electrode-skin impedance. Calibrated headphones will be placed carefully. The participant will be asked to remain seated and still during evaluation. This process will be applied for the pre and post training assessment.

As shown in Fig 4. basal state will be recorded for 60 s in opened and closed eyes conditions. Then oddball paradigm will be used to assess auditory discrimination in pitch, intensity, duration and localization of the stimuli. P300 & Mismatch Negativity Potentials will be assessed by this paradigm in attentional and non-attentional conditions.

**Fig 4 pone.0313478.g004:**
[figure not shown]
Auditory discrimination paradigm procedure. Basal state is only recorded at the beginning of the session. In each of the feature variation the rest of the procedure is repeated.

Sound system used for stimuli is integrated by a sound interface (DAC/ADC) with supra-aural Shure SRH 440’ headphones system calibrated to audiometric reference of 1kHz to 70 dB HL. Sound stimuli consists in pure tones lasted with 100 ms duration and with a 900 ms ISI as the standard stimuli. Deviant stimuli vary in each of the four testing sound features (pitch, intensity, duration and localization). EEG event related activity will be processed in Matlab with EEGLab, for preprocessing and epoching (−200ms, 600ms)”.

For the AT, digital tools will be shown to participants, they will be instructed in how to use it, and main features will be explained. They will be told to use it daily for 30 minutes indicating the modules to evaluate in each week sessions. Game data (training time, response time and correct responses) will be gathered for participants after each week to register in-game indicators. They will be asked not to do more or less time than indicated, if indication is not followed, they will not be eligible to continue participating. An extra explanatory video will be provided with a user manual.

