#### Aim.

In the light of the evidence, the aim of this research is to determine whether differences in user experience between the two systems; a game-based auditory discrimination training program and a non-game-based auditory discrimination training program, lead to differences in auditory discrimination perceptual, behavioral and electrophysiological performance within a normal-hearing population To meet this aim, the research will be conducted as follows:

To develop and validate a digital game-based auditory discrimination training tool.To develop a weekly program and to monitor key performance indicators (KPIs) in terms of time, accuracy and discrimination thresholds.To measure auditory processing improvement through perceptual, behavioral and electrophysiological tests comparing discrimination tasks’ performance before and after the use of auditory discrimination training system.

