## Methods

### Sample size, inclusion & exclusion criteria

Sample Size is determined by two means; literature has worked with sample sizes averages between 10–40 participants, due to the long training period and evaluation requirements [30,31]. Sample size was calculated determining F-tests family for ANOVA repeated measures between and within interactions, given a moderate effect size of 0.25, alpha error prob of 0.05 and power of 0.80, two groups and two measurements. Effect size was determined with related previous works, where effect sizes of behavioral auditory discrimination measurements are reported from moderate to large, based on Cohen’s d and Cohen’s f calculations [32–35]. Larger effects sizes have been suggested when individuals were submitted for first time to auditory devices [36].

G*Power 3.1 points a total sample size for both groups of 34. Considering two independent groups for auditory discrimination training (ADT) implementation, sample size for Group A (control), and Group B (experimental) will be equally distributed.

A total of 40 participants will be recruited and enrolled in the study, as described in Fig 1, predicting a sample rejection of ~10%. Each of them will be randomly assigned to one of two groups (control group or experimental group) depending on the training methodology they will receive. Sample size for each group (non-game-based ADT and game-based ADT) is 20 individuals each. Assignments of each participant will be randomized using simple randomization 1:1 allocation ratio to select the group for the training methodology, avoiding bias on trials.

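### Participants who train more or less than told are removed after randomisation, with no stated post-training assessment, so the main comparison may become one of selected completers

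*Protocol article*

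**What the plan says.** **Order of events.** Under Study design & setting, "Eligibility screen, informed consent and pure tone audiometry will be carried before allocation". Training comes afterwards: "In 30-minutes sessions (15 hours total), the 40 participants will be treated by ADT", and "They will be told to use it daily for 30 minutes".

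**The rule.** In the same section, after Fig 4, participants are asked to train for neither longer nor shorter than told, and "if indication is not followed, they will not be eligible to continue participating". No tolerance is given. The text does not say whether a person removed in this way returns for the post-training assessment.

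**What the game is for.** Materials states that "ADT Game will be developed to enhance user experience and favor attention through task engagement". The aim is to "determine whether differences in user experience between the two systems" lead to differences in performance. The introduction credits gamification with better user retention. Time in each activity is a secondary outcome (Expected outcomes & analysis).

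**Analysis.** A two-way repeated-measures ANOVA uses values before and after training, and the comparison of game with non-game training is named as the main one.

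**Sample size.** G*Power gives 34 in total. Forty are enrolled, "predicting a sample rejection of ~10" per cent. The Discussion describes the same margin as 10% withdrawal and concedes that the rate could differ. Neither place mentions removal for training time.

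**The concern.** Randomisation makes the two groups comparable at allocation. A rule that later removes people for what they do during training keeps that comparability only if it acts alike in both arms. Here the removing behaviour is time spent training, and the protocol itself expects the arms to differ in engagement. A plain tool may lose its less motivated users through under-training. A game may lose keen users through over-training. Either way, those left in each arm are selected, possibly in different ways, and the difference between them mixes the effect of the game with the effect of the selection.

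The second stake is numbers. Removals add to ordinary withdrawal, and the protocol does not say whether the allowance of about 10% covers both.

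**Working it through.** **1. Reproduce the planned size.** Inputs from Sample size, inclusion & exclusion criteria: f = 0.25, alpha 0.05, power 0.80, two groups, two measurements. The correlation between measurements is not given, so 0.5 is assumed. The noncentrality is lambda = f² × N × m / (1 − rho), with 1 and N − 2 degrees of freedom.

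- N = 34: lambda = 0.0625 × 34 × 2 / 0.5 = 8.5, power 0.807. The stated 34 is reproduced.
- Other correlations give other sizes: 66 at rho = 0, 46 at 0.3, 22 at 0.7.

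**2. Check the allowance.** 34 / 0.90 = 37.8, so 38 would cover 10% loss. Forty enrolled leave 36 after 10% loss, and break-even is 1 − 34/40 = 15%. The allowance is arithmetically sound.

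**3. Power by number analysed (rho = 0.5).**

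| Analysed | Loss | Power |
|---|---|---|
| 40 | 0% | 0.869 |
| 36 | 10% | 0.830 |
| 34 | 15% | 0.807 |
| 32 | 20% | 0.781 |
| 30 | 25% | 0.753 |
| 30, split 12 v 18 | 25% | 0.736 |

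**4. Loss under the strictest reading.** 15 h / 0.5 h = 30 sessions. Assume that any one deviant day ends participation and that days are independent with the same breach rate for everyone. The share left is (1 − breach rate)^30.

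- 0.5% per day: 0.995^30 = 0.860, about 34 of 40.
- 1% per day: 0.99^30 = 0.740, about 30 of 40.
- 2% per day: 0.98^30 = 0.545, about 22 of 40.
- Daily compliance needed to keep 34: (34/40)^(1/30) = 0.9946.

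The documents give no breach rate, so these figures are illustrations.

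**5. Bias from unequal removal.** Assume no true effect, that the least motivated are removed (30% of controls, 10% of the game arm), and that motivation correlates r with improvement. Removing the lowest fraction p of a standard normal raises the mean of the rest by phi(z_p) / (1 − p).

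- p = 0.30 gives 0.497; p = 0.10 gives 0.195.
- r = 0.3: 0.149 − 0.059 = 0.09 SD in favour of control.
- r = 0.5: 0.248 − 0.098 = 0.15 SD in favour of control.

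A simulation with 20 per arm and no true effect, keeping 12 controls and 18 in the game arm, gave a shift of 0.13 to 0.23 SD and a type I error of about 0.07 to 0.10 for r = 0.3 to 0.5. Reversing the split reversed the sign. Keeping 18 in each arm gave essentially no bias in this model.

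**6. Scale.** At rho = 0.5 the planned effect is a between-arm difference of 1.0 SD of change: d² × N/4 = 8.5 at N = 34 gives d = 1.0. A shift of 0.09 to 0.15 SD is 9 to 15% of that.

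**The case against.** **The rule may be milder than it looks.** A reader might infer that one missed or overlong day ends participation. The text does not say so. AT experimental design speaks of an equivalent of 15 hours, data are gathered weekly, and the Discussion says monitoring will be weekly. The gift card rewards daily training, a condition that would be partly redundant if any lapse already meant removal. This stands, and the retention figures in step 4 describe only the strictest reading.

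**Non-adherence is already discouraged.** People who cannot give the required time are excluded, eligibility is screened before allocation, and the gift card rewards consistent training. All of this should reduce breaches. None of it makes those that remain equal between arms.

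**Breaches cluster in a few people.** If 90% of participants breach on 0.1% of days and 10% on 9.1%, the mean is still 1%, but retention is 0.9 × 0.999^30 + 0.1 × 0.909^30 = 0.88, about 35 of 40. A reader might infer that the trial will fall below 34. The documents do not support that: 40 tolerate 15% loss, the rejection allowed for may already include removals, and the Discussion concedes that the rate is uncertain.

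**The bias is modest and rests on assumptions.** It is small beside a planned difference of 1.0 SD, and its inputs are not in the documents. A reader might infer that the game's effect will be understated. Removal for over-use could push the other way, so no direction can be claimed.

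**Equal dose is a legitimate aim.** It is. But dropping those who deviate does not recover the comparison at equal dose among randomised groups. It compares whoever stayed. The instruction, the training logs and an adherent-only analysis can serve that aim without ending measurement.

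**Analysis sets belong in the analysis plan.** They do, and their absence here is no fault. But no analysis plan can recover post-training evoked potentials that were never recorded. That removed participants miss this assessment is the natural reading of the rule, not an explicit statement.

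**Conclusion.** The point holds as a defect in a stated rule. The protocol allows removal after allocation, on a behaviour the game is meant to influence, and does not say that measurement continues. The pre/post ANOVA needs the post-training value, so the main between-arm comparison may rest on selected completers. That conclusion needs none of the illustrative figures.

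The size and direction of the bias are unknown. The range of 0.09 to 0.15 SD depends on 30% v 10% removal and a correlation of 0.3 to 0.5, all assumed. The allowance of about 10% is not miscalculated. The fault is that the rule is a further source of loss not linked to it, and whether losses pass 15% depends on how strictly the rule is enforced.

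**What to change.** Keep whatever training-time instruction is chosen, but separate it from measurement. Suggested wording:

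> All randomised participants are invited to the post-training AEP and ADPQ assessment and analysed in the arm assigned, whatever their training time. Logged training time is reported by arm. An analysis limited to adherent participants is supportive.

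Reconcile the sample-size section, the removal rule and the withdrawal statement in the Discussion, so that it is clear whether removals count within the allowance of about 10%.

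**Cost.** A change of wording and a few post-training sessions, already within the planned 40. The estimate will then include the effect of non-adherence, which should be said when it is reported. With all 40 assessed, power is 0.869 under the assumptions in step 1, for the planned effect. If non-adherence makes the as-assigned effect smaller, power will be lower than that.

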### AT experimental design

AT for both groups will contain the same four modules related to auditory discrimination tasks. Each module consists of one basic acoustic feature (pitch, intensity, duration, and localization). Participants will solve pure tone discrimination tasks identifying feature differences between acoustic stimuli A from B (reference tone), and answer whether stimuli feature was higher or lower. Reference tones are centered around 0.5, 1, 2 and 4 Khz with duration of 100 ms (fade in and fade out of 5 ms). Both groups will have auditory training for an equivalent of 15 hours, with daily monitoring data and gathered every week. Training will be applied with measured and calibrated headphones given to the participants.

#### Group A (Control).

AT for non-game-based group will consist in a simple graphic user interface. Instructions will be displayed, and once the features are selected, the user will start training getting basic feedback of wrong and right answers.

#### Group B (Experimental).

AT for game-based group will have game elements and competing resources, such as game objective, game characters and visuals, CPU competition players, feedback, time and lives management.

AT methodologies to be used are non-game based auditory training and game-based auditory training. Each tool is applied as indicated in the SPIRIT checklist in Fig 1.

### Ethical considerations & data management

This study conforms to the declaration of Helsinki and has been approved by the Ethical Committee Instituto Tecnologico y de Estudios Superiores de Monterrey Engineering School with ID EHE-2023-11. Research was also registered with the International Standard Randomized Controlled Trial Number ISRCTN43661994 on January 26^th^ 2024, for research transparency. Recruitment of participants in the study is completely free and voluntary. Enrollment will start on January 2025, expecting the end of data collection by the end of July 2025. Before any assessment participants will be explained about research procedures and written informed consent will be delivered and signed by each participant, who can ask for a copy if it is desired.

For correct management of the participants’ information the following points will be accomplished all during the assessment sessions period.

Recruited participants will be completely voluntary.Assessment registers will be done in Tec de Monterrey so it will not be necessary to attend to another place.Participation will be completely free. Material will be proportionated to applicants.Individual evaluations and assessments will be given to volunteers.Volunteers will receive the information and explanation of each step before, during and after the training to guarantee uniformity and informed participation.Participants will sign an informed consent format before the session begins. Participants will receive a copy of the consent. This information will be kept by the applicants and can be consulted for any investigation purpose.Participants’ identity will remain anonymous. Participants’ information will be treated with complete confidentiality.Applicants will count with disposition towards the participants for evaluation purposes.Participants’ information will be delivered only to the institution and legal authorities if required.

All registers and assessments including audiometry and AEPs are non-invasive, which will not place participants at higher risk other than listening. To minimize risk of placing participants to high sound pressure level for a long period of time, sound pressure level will be fixed within the equipment to use so that they would not exceed suggested sound levels.

Any medical or clinical occurrence related or not with the research procedure, will be managed as an adverse event, and treated or reported according to institutional health services protocol, mainly considering participant safety and health. Adverse events will be further evaluated for participant continuity in the research experiment.

### Expected outcomes & analysis

The primary outcome measures are related to neuro audiological changes in auditory processing. AEPs to be obtained are Mismatch Negativity and P3 components (continuous). Additionally, number of discrimination trials (discrete) will be registered. The secondary outcome measures are the in-game indicators such as time in each activity (continuous), accuracy (discrete) and attempts (discrete) to relate directly changes in audiological measures and game performance. The expected outcome of ADPQ is to increase the average score, that indicates a better perceived state and performance in auditory discrimination tasks that would be correlated with the in-game indicators and the electrophysiological measurements. The expected comparison outcome for AEP, it is expected an increase in evoked potentials amplitude and a decrease in latencies. For the in-game indicators it is expected to increase accuracy answers and decrease tasks’ solving time.

Once obtained and processed KPIs and discrimination threshold results, data will be analyzed with the following tools. Each of them will compare before and after auditory training KPIs and AEPs tests.

A 2-way analysis of variance (ANOVA) with repeated measures will be done considering the following factors.

For pre & post training measurements to determine individual performance of each methodology and contrast the improvement of each (within factors).For training group. Both methodologies have a similar distribution of activities to accomplish withing the training. Each group will be evaluated to determine if some activity yielded to a more significant difference in the overall performance (between factors).Finally, and mainly, for AT methodology groups to analyze and compare the final performance between the game-based experimental groups and the non-game-based control group and conclude if there is a significant difference between them.

The following cases are proposed to test main 2-way ANOVA with repeated measures assumptions (normality, sphericity and equal variance) [37,38]. Normal distribution will be addressed using a histogram and Shapiro-Wilk test. If no normal distribution is found, data transformation (log or sqrt) will be conducted to repeat the normality test. Treating Type I errors of heteroscedasticity, sphericity would be addressed through a Maulchy’s test. If no sphericity was found, Greenhouse-Geisser correction would be conducted to adjust degrees of freedom and repeat sphericity test. Since this study within-subjects factor (repeated measures) is only having two measurements, sphericity assumption is not required due to no covariance comparisons. If normal distribution is not corrected, repeated measures ANOVA non-parametric equivalent test will be used (Friedman’s test). An additional Barlett’s test would be done for equal variance assumption if ANOVA normality is confirmed. If equal variance is violated, robust ANOVA may be considered.

Bonferroni post-hoc test will be conducted, using multiple t-tests times p-values (to avoid increase in alpha error). Analysis software to be used is Minitab with a level of significance of 0.05.

Possible spillover effects that could bias primary outcome measures are related to 3 main conditions:

Participants discrimination performance: This effect is considered through a discrimination performance questionnaire that the participant answer to address biases during tests of outcome measures.Participants health condition (auditory pathways related): This effect is addressed through rescheduling the tests when hearing health condition is better.Participants simultaneous training: This effect is addressed in the inclusion criteria where no additional formal auditory training is performed by the participant at the time of intervention.

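### Several evoked-potential measures are primary at 0.05 with no adjustment across them, while the sample size is for one test

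*Protocol article*

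**What the plan says.** All references are to the Protocol article.

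- **Primary outcome** (Expected outcomes & analysis): "The primary outcome measures are related to neuro audiological changes in auditory processing". The measures are then given: "AEPs to be obtained are Mismatch Negativity and P3 components (continuous"). The next sentence adds a count: "Additionally, number of discrimination trials (discrete) will be registered".
- **Parameters** (same section): for the evoked potentials, "it is expected an increase in evoked potentials amplitude and a decrease in latencies".
- **Features** (Study design & setting, text after Fig 3): "oddball paradigm will be used to assess auditory discrimination in pitch, intensity, duration and localization of the stimuli".
- **Conditions** (same place): "P300 & Mismatch Negativity Potentials will be assessed by this paradigm in attentional and non-attentional conditions".
- **Electrodes** (same place): "Electrodes (Fz, F3, F4, Cz, C3, C4, T7 & T8) will be placed".
- **Level** (Expected outcomes & analysis): "Analysis software to be used is Minitab with a level of significance of 0.05". The sentence before it provides Bonferroni-multiplied t-tests as a post-hoc step. No adjustment across outcome measures is described.
- **Sample size** (Sample size, inclusion & exclusion criteria): 34 in total from G*Power for a repeated-measures between-within interaction, with effect size 0.25, alpha 0.05, power 0.80, two groups and two measurements. Forty are to be enrolled, allowing for about 10% loss.

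**The concern.** No component, parameter, feature, condition or electrode is singled out as the one on which the trial will be judged. The analysis section does give priority to a contrast, game-based against non-game-based training, but leaves open the measure to which it applies.

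The Bonferroni step does not fill the gap. In a design of two groups by two times, a post-hoc t-test adjusts comparisons among cells of one ANOVA on one outcome. It does not adjust for running a further ANOVA on P3 latency after one on mismatch negativity amplitude.

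Two things are at stake. A significant result on any one component, parameter or feature could be reported as the primary finding, with an error rate well above the stated 5%. If the correction is made only afterwards, power falls below the planned 0.80, because the sample size allows for a single test. The article also states that those who analyse the data are not blinded, so a choice of measure fixed in advance is the main protection against selection.

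**Working it through.** **1. Reproduce the planned sample size.** Inputs from the article: f = 0.25, alpha = 0.05, power 0.80, k = 2 groups, m = 2 measurements. The article gives no pre-post correlation; 0.5 is assumed. For the within-between interaction:

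λ = f² × N × m / (1 − ρ), df1 = (k − 1)(m − 1) = 1, df2 = (N − k)(m − 1) = N − 2.

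At N = 34: λ = 0.0625 × 34 × 2 / 0.5 = 8.5, df2 = 32, power 0.807. At N = 32, power is 0.781. So 34 is reproduced, as a single test at 0.05. Under other correlations the required total would be 46 (ρ = 0.3), 22 (0.7) or 16 (0.8).

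**2. Count the tests.** The article gives no count, so two readings are taken:

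- features pooled: 2 components × 2 parameters = 4;
- features separate: 2 × 2 × 4 = 16.

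Attention conditions, electrodes and the trial count are left out of both.

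**3. Familywise error**, if no true effect exists and any one significant measure may be claimed. For independent tests it is 1 − 0.95^k: 1 − 0.95^4 = 18.5% and 1 − 0.95^16 = 56.0%. For correlated tests, two-sided normal tests with a common correlation r were simulated (200,000 draws).

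| Tests | Independent | r = 0.3 | r = 0.5 | r = 0.7 |
|---|---|---|---|---|
| 4 | 18.5% | 17.2% | 15.6% | 13.1% |
| 16 | 56.0% | 47.5% | 37.4% | 26.4% |

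**4. Power if Bonferroni is applied across the primary measures.** Same formula as step 1, ρ = 0.5, with alpha 0.05/4 = 0.0125 or 0.05/16 = 0.003125. The column for 36 is the number expected after the planned loss: 40 × 0.90 = 36.

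| Tests | N = 34 | N = 36 | N = 40 | Total N for 0.80 |
|---|---|---|---|---|
| 1 | 0.81 | 0.83 | 0.87 | 34 |
| 4 | 0.61 | 0.64 | 0.70 | 48 |
| 16 | 0.41 | 0.44 | 0.51 | 64 |

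**The case against.** **The test count is inferred.** This stands. The article lists electrodes as placed, not as endpoints, and says that features and conditions are assessed, not that each has its own primary test. Components might be paired with conditions, features pooled or electrodes averaged. A reader might go further and count 32 tests by treating each attention condition separately (81% if independent, 52% at r = 0.5, 35% at r = 0.7), or multiply again by eight electrodes. The text does not support stating either as the plan. It is also unclear whether the discrimination-trial count is primary.

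**A false positive need not be likely.** This also stands. Measures from the same recordings in the same people would be expected to correlate. A chance above one half needs 16 near-independent tests, or 32 with correlation up to about 0.5.

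**Success might require the whole expected pattern**, larger amplitudes together with shorter latencies, in which case the error would not inflate. But the article states that pattern as an expectation and nowhere makes the conclusion depend on all of it. The error figures are therefore conditional on a claim from any one measure.

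**The Bonferroni sentence names no family**, and its stated purpose is to limit alpha error. It might be meant more widely. Pairwise t-tests after an ANOVA remain the natural reading, and if it did cover all primary measures, the power in step 4 would apply instead.

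**A separate analysis plan may order the endpoints.** It may, and the details can be left there. What the protocol itself fixes (plural primaries, 0.05, a post-hoc correction only, a size for one test) still does not fit together. Even two tests, one per component, give 9.8% if independent and 8.3% at r = 0.7.

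**Conclusion.** The point holds in a limited form. As written, the plan lets the error across its primary measures exceed 5% on every reading with more than one primary test: about 13–19% for 4 tests and 26–56% for 16, over correlations from 0.7 down to independence, provided that any one significant measure may be claimed. That proviso and both counts are assumptions.

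A reader might infer that the sample size is miscalculated. It is not: 34 is reproduced at a pre-post correlation of 0.5, and 40 covers the stated loss (34 / 0.90 = 37.8, so 38). Its limit is that it serves one test. Nor does every correction leave the trial at even odds. At the expected 36 participants, power per measure is 0.64 for 4 tests and 0.44 for 16, under plain Bonferroni and the same assumed correlation.

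**What to change.** Before any post-training evoked-potential data are analysed, name one primary measure in the protocol: component, parameter, attention condition, electrode or electrode average, and how the four features are combined. The choice is the sponsor's. Make the group-by-time interaction on that measure the single primary test at 0.05. Make the other evoked-potential measures of interest and the discrimination-trial count secondary, with Holm adjustment across a short listed set, and the remainder exploratory without claims of significance. The deadline has to be tied to the data, because the analysts are not blinded and there is no unblinding step to use.

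Alternatively, keep several primaries, list them as a defined family, apply Holm or Bonferroni across it and restate the power with the assumed pre-post correlation given.

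The first option costs wording and a matching change to the registration if needed, and it keeps 34 valid. Its downside is that fewer results can be called primary. The second costs power or participants: under plain Bonferroni with the article's inputs and ρ = 0.5, the total would be 48 for 4 measures and 64 for 16.
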